#### Statistical power

Sample sizes of 75 in Group 1 and 75 in Group 2, which were obtained by sampling 15 clusters with an average of five subjects each in Group 1 and 15 clusters with an average of five subjects each in Group 2, achieve 84% power to detect a difference between the group means of at least 25.00 days of registered sickness absence 1 year after baseline. The standard deviation of subjects is 50.00. The intra-cluster correlation coefficient is 0.010. The coefficient of variation of cluster sizes is 0.650. A two-sided t-test was used with a significance level of 0.050. This test used degrees of freedom based on the number of subjects. No missing values are expected since the primary outcome is based on register data. The aim of the current study is therefore to include a total of 150 participants.

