## Methods

### Study design and setting

The study has a two-armed cluster randomized controlled design with a primary follow-up period of 1 year (see Fig. 1). The study is conducted in collaboration with three OHSs in Sweden. One OHS has nationwide coverage while two are regional OHSs. Each participating OHS consultant is considered as one cluster. The participating OHS consultants consist of occupational nurses, physicians, physiotherapists, ergonomists, occupational health counselors and psychologists.

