### Randomization

The study uses a two-armed cluster randomized design in which the participating consultants are randomized using computer-generated random numbers into either giving the intervention or performing care as usual. Hence, each OHS consultant has to continuously apply the same treatment within the context of this study. The randomization is stratified by OHS unit as well as by occupational category, as those two factors are assumed to have a potential impact on the results and a balance within strata is necessary.

It was not feasible to randomize employees between OHS consultants trained or not trained in the intervention, because different employers have contracts with different OHS consultants, that is, a certain employee is linked to a certain OHS consultant. An alternative may have been to train all OHS consultants in the intervention, however, this should have increased the risk of contamination.

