### Data analysis

Statistical methods adapted for cluster randomized designs will be applied. The plan is to apply various forms of regression models and mixed models. Intention-to-treat analyses will be carried out. Where relevant, per-protocol analyses will also be performed. If it appears that potential confounders have been unevenly distributed and can be expected to affect the results when the two interventions are compared, these factors will be adjusted for in the analyses. Possible interaction effects on the outcome for (1) gender x treatment (intervention) and (2) sick leave status (sick leave/no sick leave) x treatment will be checked for. If they are statistically significant, subgroup analyses will be considered.

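### The 84% power is computed on subject-based degrees of freedom although 30 consultants are randomised; on 28 cluster-based degrees of freedom it is about 82%

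*Protocol article*

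**What the plan says.** The Study design and setting section defines the cluster: "Each participating OHS consultant is considered as one cluster". The Randomization section makes the same people the units of allocation: "the participating consultants are randomized using computer-generated random numbers into either giving the intervention or performing care as usual".

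The Statistical power section assumes "15 clusters with an average of five subjects each in Group 1" and "15 clusters with an average of five subjects each in Group 2", that is, 75 employees per arm. These numbers are said to "achieve 84% power to detect a difference between the group means of at least 25.00 days of registered sickness absence 1 year after baseline". It adds "The standard deviation of subjects is 50.00", an intra-cluster correlation of 0.010, a coefficient of variation of cluster sizes of 0.650, and a two-sided t-test at the 0.05 level. It then states the basis of the reference distribution: "This test used degrees of freedom based on the number of subjects".

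On the analysis itself, the Data analysis section says "Statistical methods adapted for cluster randomized designs will be applied" and names regression and mixed models. It gives no rule for degrees of freedom.

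**The concern.** A power calculation for a cluster randomised trial has to allow for clustering in two places. One is the variance of the treatment contrast, which the design effect inflates. The other is the reference distribution, which should reflect how many independent units provide the estimate of that variance. The protocol does the first and not the second. Its variance recognises that employees are grouped under consultants, but its t distribution has the degrees of freedom of a trial that randomised 150 employees individually.

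With only 30 randomised units the two t distributions differ visibly: the two-sided 5% critical value is 1.976 on 148 degrees of freedom and 2.048 on 28. The lower value makes the power look higher than a cluster-based test would deliver. What is at stake is the accuracy of the headline power for the primary outcome and, if the rule were reused when the data are analysed, the nominal error rate of some forms of the primary test.

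**Working it through.** **Inputs** (all from the Statistical power section): difference 25 days; SD 50; 15 clusters per arm; mean cluster size 5, so 75 employees per arm; ICC 0.010; CV of cluster sizes 0.650; two-sided alpha 0.05.

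**Design effect for unequal clusters**

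1 + [(CV² + 1) × m − 1] × ICC = 1 + [(0.4225 + 1) × 5 − 1] × 0.010 = 1 + 6.1125 × 0.010 = 1.0611.

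The relative-efficiency form of the correction gives 1.0605, and the choice between the two does not affect the result.

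**Standard error and noncentrality**

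SE = 50 × √(2 × 1.0611 / 75) = 8.41 days.

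Noncentrality = 25 / 8.41 = 2.97.

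**Reproducing the stated figure, then changing only the degrees of freedom** (two-sided noncentral t)

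| Basis | Degrees of freedom | Critical value | Power |
|---|---|---|---|
| Subjects (as stated) | 150 − 2 = 148 | 1.976 | 84.0% |
| Clusters | 30 − 2 = 28 | 2.048 | 81.8% |

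The printed 84% is reproduced on 148 degrees of freedom. With everything else held fixed, 28 degrees of freedom lowers it by about 2 points.

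**Difference detectable with 84% power on 28 degrees of freedom**

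The required noncentrality is 3.06, and 3.06 × 8.41 ≈ 25.7 days.

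**Conditional check on the type I error**

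If a statistic that truly has 28 degrees of freedom is compared with the 148-degree critical value, the two-sided error is P(|T₂₈| > 1.976) = 5.8%.

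Null simulations with normal data, 30 clusters of mean size 5 and the stated ICC and CV gave:

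| Test | 148-df critical value | 28-df critical value |
|---|---|---|
| Size-weighted cluster-level t-test | about 6.0% | 5.2% |
| REML random-intercept model | about 4.7% | about 4% |

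So the direction and size of any effect on the error rate depend on which test is used.

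**The case against.** The defence has real substance. The 84% follows correctly from the listed inputs, and the basis for the degrees of freedom is disclosed rather than hidden. The loss is about 2 points, power remains above 80%, and no design decision changes. With an ICC of 0.010 and clusters of about five, most of the variance of the contrast lies within clusters. A Satterthwaite-type calculation would therefore estimate the degrees of freedom from the data rather than fix them at 28. All of this stands, and it limits the weight of the point.

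Three stronger readings are tempting, and the protocol does not support them.

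- **That the trial's type I error is inflated.** The sentence on degrees of freedom describes the power calculation. Nothing says that the rule will be used in the analysis. In a mixed model, one of the types of model the protocol names, simulation at the stated ICC showed no inflation with the subject-based critical value.
- **That the power calculation contradicts the Data analysis section.** That section promises cluster-adapted methods and sets no rule for degrees of freedom. A calculation that already carries a design effect does not conflict with it. A detailed rule for the primary model may properly sit in an analysis plan that is not shown.
- **That the trial is underpowered.** On the protocol's own inputs, 28 degrees of freedom still give more than 80%. A lower figure would need a larger ICC, or degrees of freedom spent on stratification factors. The protocol states neither, and the choice of ICC is a separate question.

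What the defence does not remove is that the reference distribution counts employees when consultants were randomised. Disclosing that choice does not make it the appropriate basis with 30 clusters.

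**Conclusion.** The point holds as a correction to a stated figure. The power of 84% rests on 148 subject-based degrees of freedom. On the 28 that follow from 30 randomised consultants it is about 82% (81.8%) for 25 days, and 84% corresponds to about 25.7 days. This takes the protocol's SD, ICC, CV and cluster numbers as given. It also assumes a two-arm comparison with cluster-based degrees of freedom and none spent on covariates.

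Severity is minor to moderate: the figure is optimistic in a known direction, the shift is small, and the sample size need not change. The type I error is a caution only. It applies if the subject-based rule is carried into a cluster-level test, where the error would be about 5.8% to 6.0% instead of 5%.

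**What to change.** In the Statistical power section, replace the sentence on degrees of freedom with one saying that they are based on the number of clusters (28). Restate the power as about 82% for a difference of 25 days or, if 84% is to be kept, give the detectable difference as about 25.7 days. The target of 150 participants and 30 consultants stays as it is.

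As a safeguard when the primary model is specified, do not carry the subject-based rule over. Use cluster-based degrees of freedom or a small-sample method such as Satterthwaite or Kenward-Roger.

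The cost is wording only, plus a stated power about 2 points lower.

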## Discussion

This study protocol presents the design of a cluster RCT performed at the OHS. The OHS is acquainted with the employee’s work environment and can offer measures that take both the individual and the working situation into account. The purpose of the evaluated intervention is to prevent sickness absenteeism and improve work ability among employees with CMDs or stress-related symptoms. The intervention’s impact on sick leave and mental health and its cost-effectiveness will be evaluated. By conducting a process evaluation of the intervention we also intend to evaluate how the treatment fidelity of the OHS-consultants may influence sickness absence outcomes among the participating employees. The process evaluation will also give information about the feasibility of the intervention and contextual factors that may have affected the implementation process, which could be useful for future applications of the intervention.

### Methodological considerations

We cannot exclude the risk of selection bias i.e. that the OHS consultants choose which employees to invite to participate in the study on the basis of, for example, how well they believe the intervention would work for a particular employee. Hence, during the training and follow-ups with the OHS consultants, we emphasize the importance of telling all employees who match the inclusion criteria about the study. We will also include an item relating to this in the process evaluation check-lists that will be distributed to the OHS consultants.

There is also risk of possible contamination of interventions because OHS consultants at the same OHS may deliver either care as usual or the experimental intervention. This concern is, similarly to the above, addressed in the training and follow-ups of the OHS consultants belonging to the intervention group, at which the reasons for not discussing the intervention contents with colleagues allocated to deliver the control condition are explained. An item on this issue will also be included in the process evaluation check-list to the OHS consultants.

In Sweden, the employer records and pays for sick leave related costs up to and including the 14th day of sick leave. For this reason, national, register-based data on sick leave maintained by the SSIA is available from the 15th day onwards, with no information available for short-term sick leave. The current study consequently sends text messages that include questions about short-term sick leave (< 15 days) to all participants once every 4 weeks. This will give valuable information about short-term sick leave among the participants. Nevertheless, the reliance on similar self-reports is subject to possible recall bias and larger drop-out rates than register-based data. To increase the response rates, we have used reminders by calling employees about missing answers; in a previous study this was found to increase response rates [45].

Two previous Swedish studies have shown that employees with CMDs may seek treatment on their own, especially if they are aware that they belong to the control group [46, 47]. To detect possible treatment bias of this sort, items on co-interventions have been included in the questionnaires to the employees. The OHS consultants have also been advised not to inform employees whether they belong to the control or the intervention group, since active workplace-focused treatments are given in both conditions.

The study population will consist of employees with reported stress-related symptoms but no sick leave at baseline and employees on sick leave due to CMDs. As mentioned earlier, possible differential effects of the intervention in these groups may arise. Potential interactions between sick leave status at baseline and the secondary outcomes will therefore be taken into account.

### Possible impact of results

For employees with mental health problems or stress-related symptoms, failure to take the work environment into account may lead to reduced work ability and repeated and/or prolonged spells of sick leave. The current intervention looks at both the individual and the workplace context. If the intervention proves successful and is implemented at large within the OHS sector, it may result in increased work ability, reduced rates of sick leave and improved quality of life among employees with CMDs or occupational stress. This may also reduce costs, both for the employer and for society at large.

## Abbreviations

CBT: Cognitive behavioral therapy
CMD: Common mental disorders
MBI-GS: Maslach Burnout Inventory - General Survey
OHS: Occupational health services
PST: Problem solving therapy
RTW: Return to work
s-ED: The stress-related Exhaustion Disorder measurement instrument
SSIA: The Swedish Social Insurance Agency
